#### (1) Definition of measurable lesion

Lesions that correspond to at least 1 of the following terms are referred to as "measurable lesions".

- 1) Lesions other than lymph node lesion (non lymph node lesions) that satisfy at least one of the following criteria:
  - ① The maximum diameter observed by CT using a slice thickness of  $\leq 5$  mm is  $\geq 10$  mm.
  - ② The maximum diameter observed by CT using a slice thickness of  $> 5$  mm is at least 2 times thicker than the slice thickness.
  - ③ Osteolytic bone metastasis lesions with soft tissue lesion(s) satisfying ① or ②.
  - ④ Cystic metastasis lesions satisfying ① or ② when there are no other measurable non-cystic lesions.
- 2) Lymph node lesions with a short diameter of  $\geq 15$  mm observed by CT using a slice thickness of  $\leq 5$  mm. Lymph node lesions with a short diameter of  $\geq 10$  mm and  $< 15$  mm are non-measurable lesions, and lymph node lesions with a short diameter of  $< 10$  mm are not lesions.
- 3) The maximum diameter observed by chest simple radiographic imaging is  $\geq 20$  mm, and the lesion is surrounded by lung tissue (i.e., the lesion has no contact with the mediastinum or chest wall).
- 4) Superficial lesions with a maximum diameter of  $\geq 10$  mm or more that can be photographed in color with a measuring ruler (cutaneous metastasis, etc.).

All lesions that do not satisfy the above terms will be referred to as "non-measurable lesions". The following lesions, etc. are referred to "non-measurable lesions" regardless of the test methods used and the size of the lesions:

- Bone lesions (except for osteolytic lesions with a measurable soft tissue component).
- Cystic lesions (except for those meeting the above criterion given in {1)-④}).
- Lesions with a history of local treatment such as radiotherapy.
- Meningeal lesions.
- Ascites, pleural effusion, and cardiac effusion.
- Inflammatory breast cancer.

- Skin/lung lymphangitis.
- Palpable abdominal tumors and abdominal organ enlargement that cannot be confirmed by imaging.

(2) Selection of target lesion and baseline evaluation

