The response rate is the rate of patients whose best overall response {3.8(6) Best overall response} in a target population with measurable lesions is CR or PR as a proportion of all the cases that underwent treatment.

(7) Health-related quality of life (HRQoL)

See "5.5 Survey of health-related quality of life".

(8) Adverse events (toxicity)

Adverse events that are observed from registration to the discontinuation of the protocol treatment will be evaluated in all treated cases (see "19 Evaluation and reporting of adverse events").

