- Presence/absence of a history of chemotherapy after recurrence (confirmation of absence)
- Organs confirmed the presence of recurrence or metastasis

C) Past medical history

② Physical findings

A) Height

B) Weight

C) Performance Status

③ Diagnostic imaging for evaluation of breast cancer lesions

The following terms will be evaluated within 28 days (within 4 weeks) before registration.

- A) Chest CT, MRI, or chest X-ray (essential)
- B) Abdominal CT, MRI, or abdominal ultrasound (essential)
- C) Bone scintigraphy when bone metastasis is clinically suspected
  - \* When bone metastasis is suspected by bone scintigraphy, bone radiography, CT or MRI, etc. is conducted to evaluate the lesion.
- D) Brain CT or MRI when clinically brain metastasis is clinically suspected.
- E) Evaluation and recording of lymph node and local skin recurrent focus
  - \* Inspection: It is favorable to observe progress using photos with indicators attached.
  - \* Palpation: The size of foci such as superficial lymph nodes and cutaneous metastases are directly measured from outside the body if the size is measurable. It is desirable to evaluate with CT and/or ultrasound when the measurement method is applicable.

④ Survey of adverse events

Adverse events of Grade 3 or higher will be confirmed in accordance with the Common Terminology Criteria for Adverse Events v4.0 Japanese translation JCOG edition, and recorded.

Especially, the presence or absence of the following adverse events, which are common symptoms in breast cancer patients and associated with endocrine therapy, will be confirmed and recorded.

When adverse events of Grade 3 or higher are confirmed for symptoms other than the followings, the symptoms as recorded as "Other adverse events".

- Constipation
- Diarrhea
- Oral mucositis
- Nausea
- Vomiting
- Malaise
- Pain
- Joint pain
- Insomnia
- Vaginal discharge
- Vaginal dryness
- Hot flash

⑤ Survey of treatment

Presence or absence of concomitant medications (use of bisphosphonate formulation or anti-

RANKL antibody), endocrine therapeutic medicines planned to be administered, scheduled day of initiation of treatment, and reasons for the selection.

⑥ Survey of HRQoL (See details for 5.5 Survey of health related quality of life)

The following questionnaire (scale) will be used to evaluate HRQoL.

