**(5) Survey planned at 3 months after the initiation of protocol treatment**

The following survey will be implemented at 3 months after the initiation date of protocol treatment:

① Physical findings

\* It is acceptable to implement the survey within 2 weeks before or after the specified day.

- A) Weight
- B) Performance status

② Diagnostic imaging for evaluation of breast cancer lesions

\* It is desirable to use the same techniques as those used for the examination implemented before registration.

\* It is recommended to implement the examination within 2 weeks before or after the specified day.

- A) Chest CT, MRI, or chest X-ray
- B) Abdominal CT, MRI, or abdominal ultrasound
- C) Bone scintigraphy when bone metastasis is clinically suspected
  - \* When bone metastasis is suspected by bone scintigraphy, bone radiography, CT, or MRI, etc. is conducted to further evaluate the lesion.
- D) Brain CT or MRI when brain metastasis is clinically suspected
- E) Evaluation and recording of lymph nodes and locally recurrent skin foci
  - \* Inspection: It is favorable to record progress using photographs with indicators attached.
  - \* Palpation: The size of foci such as superficial lymph nodes and cutaneous metastases will be directly measured from outside the body if their sizes are measurable. It is desirable to use CT and/or ultrasound for evaluations where applicable.

③ Survey of adverse events

The presence or absence of adverse events of Grade 3 or higher occurring within the past 3 months will be confirmed and recorded.

\* It is acceptable to implement the survey within 2 weeks before or after the specified day.

The contents of survey are the same as specified in ④ of 5.4 (3). The survey must be completed before registration.

④ Survey of treatment state

- A) Presence or absence of discontinuation of the protocol treatment and the reasons and date of discontinuation if discontinued
- B) Compliance with the protocol treatment for the past 3 months

- C) Presence or absence of use of bisphosphonate formulation or anti-RANKL antibody for the past 3 months
  - D) Presence or absence and reasons for implementation of concomitantly used therapies (surgical therapy for breast cancer focus, radiotherapy for breast cancer focus, any molecularly-targeted drugs other than mTOR inhibitors, chemotherapy, immunotherapy, other drugs recognized to have antitumor activity against breast cancer) for the past 3 months
- ⑤ Survey of HRQoL {the same as 5.4 (4) ①}

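### The measurable-lesion definition omits MRI although the imaging schedule accepts MRI in place of CT, so a patient measurable only on MRI has no target lesion and cannot be rated PR or SD

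*Protocol*

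**What the plan says.** **What counts as measurable (Protocol 3.8 (1)).** There are four routes:
- Non-nodal lesions qualify by CT: "The maximum diameter observed by CT using a slice thickness of" 5 mm or less must reach 10 mm or, with thicker slices, twice the slice thickness. The bone and cystic items refer back to these two CT rules.
- Nodes qualify by a short diameter of at least 15 mm on CT.
- Lung lesions qualify on chest radiograph at 20 mm or more.
- Superficial lesions of at least 10 mm qualify if they are of a kind "that can be photographed in color with a measuring ruler".

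The list is then closed with "All lesions that do not satisfy the above terms will be referred to as" non-measurable. Neither MRI nor ultrasound is named.

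**What imaging is accepted (Protocol 5.4).** The mandatory baseline chest examination may be CT, MRI or X-ray. The abdominal one is "Abdominal CT, MRI, or abdominal ultrasound (essential"). The 3-month and 6-month surveys repeat the choice: "Abdominal CT, MRI, or abdominal ultrasound". Section 3.8 (4) asks that follow-up use the method used before registration, so a baseline MRI carries forward.

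**How ratings follow.** Target lesions are drawn only from measurable lesions (3.8 (2)). Response rate counts patients whose best response "in a target population with measurable lesions is CR or PR", as a proportion of all treated cases (3.9 (6)). The first sentence of 3.9 (1) defines clinical benefit as no progression for 6 months. The second spells this out as a time point response of CR, PR or SD with no clinical progression.

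**The concern.** The schedule treats MRI and CT as interchangeable, but the response rules do not. A site can follow 5.4 exactly, image a large liver metastasis by MRI, and find that 3.8 (1) makes it non-measurable; on CT the same lesion would be a target lesion. For a patient with no other target lesion, the choice of scanner then decides which response categories are open to her.

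Two endpoints are touched. Response rate is secondary and loses responders who cannot be rated PR. Clinical benefit rate is primary and is tested against 30%. It loses stable patients if the second sentence of 3.9 (1) is applied literally. Section 6.2 (2) admits patients with or without measurable lesions, so nothing at entry screens such patients out.

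**Working it through.** **1. The same lesion followed through the protocol, with no other target lesion present**

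| Step | Imaged by CT, size rule met | Imaged only by MRI |
|---|---|---|
| Measurable, 3.8 (1) | Yes | No |
| Status, 3.8 (2) and (3) | May be a target lesion | Non-target |
| Ratings for the lesion, 3.8 (4) | CR, PR, SD, PD, NE | CR, Non-CR/non-PD, PD, NE |
| Overall rating, 3.8 (5) | CR, PR, SD, PD, NE | CR, Non-CR/non-PD, PD, NE |
| Stable 6 months: benefit by 3.9 (1), first sentence | Yes | Yes |
| Stable 6 months: benefit by 3.9 (1), second sentence | Yes (SD) | No |
| Can enter the response-rate numerator, 3.9 (6) | Yes | No |

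With a second lesion that qualifies by CT, radiograph or photograph, the target-lesion table of 3.8 (5) applies and PR and SD are reachable again.

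**2. The plan's own sample size**

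Inputs from 7.3 and 5.10 (3): threshold 30%, expected 50%, one-sided 5%, power 80%, exact binomial test. The rejection limit r is the smallest value with P(X ≥ r | n, 0.30) ≤ 0.05.

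- n = 43: r = 19, attained level 0.0342, power P(X ≥ 19 | 43, 0.50) = 0.820. The stated 43 is reproduced. It is the smallest n from which power stays at or above 80%; 39 and 41 also reach it, but 40 and 42 do not.
- Dropout: 43 / 0.90 = 47.8, so 48. The plan sets 50.
- n = 50: r = 21, attained level 0.0478, power 0.899.

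**3. Effect on clinical benefit rate if the second sentence of 3.9 (1) governs**

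Let f be the share of truly benefiting patients who have no target lesion because of the MRI gap and stay Non-CR/non-PD. The protocol gives no value, so f is an assumption. Counted rate = 0.50 × (1 − f). Power is P(X ≥ r) at that rate, with r = 19, 21 and 72 for n = 43, 50 and 200.

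| f | Counted rate | Power, n = 43 | Power, n = 50 | Power, n = 200 (all cohorts) |
|---|---|---|---|---|
| 0 | 50% | 0.820 | 0.899 | 1.000 |
| 5% | 47.5% | 0.721 | 0.821 | 1.000 |
| 10% | 45% | 0.601 | 0.714 | 0.996 |
| 20% | 40% | 0.340 | 0.439 | 0.891 |

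If the first sentence governs, f is 0 and the top row applies.

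**4. Effect on response rate**

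Assume a true rate of 20% and let g be the share of responders lost. With all treated cases as denominator, the counted rate is 20% × (1 − g): 18%, 16% or 14% at g = 10%, 20% or 30%. If the denominator is patients with measurable disease, as the opening of 3.8 can be read, these patients leave both numerator and denominator. The rate then stays at 20%, provided modality is unrelated to response.

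**The case against.** - **The reference to RECIST 1.1.** Section 3.8 opens with lesions measurable by that guideline, so MRI may have been intended. The guideline is not at hand, and the protocol writes out its own list with a catch-all. A site following that text must exclude MRI. The objection suggests an oversight but does not remove it.
- **Survey imaging is not measurement.** Section 5.4 keeps examinations within regular practice, and nothing says every accepted scan must yield a measurable lesion. That is true. But the 3-month and 6-month ratings rest on this imaging, and 5.4 gives no sign that MRI ranks below CT.
- **Ultrasound.** A reader might infer that its omission is the same defect. The documents do not support this: 3.8 (7) places ultrasound among the other methods for judging clinical progression, so leaving it out of measurement appears deliberate.
- **Any lesion followed by MRI.** A reader might infer that every patient with such a lesion is barred from PR or SD. The bar applies only where there is no other target lesion.
- **The source of the power loss.** The loss in step 3 arises because 3.9 (1) does not list Non-CR/non-PD. That omission affects every patient without target lesions, including those with bone-only disease. This stands: the MRI gap adds patients to a wider defect and is not its cause.
- **Differential bias between drug cohorts.** A reader might infer this too. The protocol gives no modality frequencies by site or drug, and 7.3 says the study does not aim to compare cohorts.

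**Conclusion.** The point holds in a limited form. The list in 3.8 (1) and the imaging accepted in 5.4 disagree about MRI. Applied as written, the list misclassifies patients whose only otherwise measurable disease was imaged by MRI. They cannot be rated PR or SD, and they are lost from the response-rate numerator while staying in the denominator if the all-treated wording of 3.9 (6) is used. Whether the primary endpoint suffers depends on which sentence of 3.9 (1) governs.

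The size is unknown. The range of f in step 3 and the values of g and true response rate in step 4 are illustrations, not estimates. At the planned 50 per cohort, a 5% share still leaves power just above 80%. Shares of 10% or 20% do not. The analysis of all cohorts together keeps power near 0.89 or better throughout the range, although its estimate would be too low by the same factor. This is a rule that needs correcting, not a flaw in the design or in the sample size: with f = 0 the stated 43 and 50 stand.

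**What to change.** 1. Add MRI to 3.8 (1), items 1) and 2), with the same size and slice-thickness rules as CT. Ultrasound can stay out.
2. Reconcile 3.8 (1) with the modalities accepted in 5.4 (3), (5) and (6), and state one denominator for response rate.
3. Reconcile the two sentences of 3.9 (1). The missing Non-CR/non-PD category needs its own correction, because adding MRI does nothing for other patients without target lesions.
4. A sensitivity analysis is optional. If one is wanted, restrict by baseline modality only, and keep patients who progressed or stopped early in the denominator. Do not require qualifying imaging at baseline, 3 and 6 months: 5.4 (6) waives the 6-month survey once progression or discontinuation is reported at 3 months. That restriction would remove early failures and inflate the clinical benefit rate.

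The cost is protocol wording. No extra scan is needed: the test method is recorded for each lesion (3.8 (2) and (3)), and the imaging performed is reported (5.7 (2) and (3)). For patients already enrolled, reclassification needs the diameters of lesions that were entered as non-target. Section 5.7 (2) asks for these measurements but 3.8 (3) does not list them, so their availability should be checked first. A restricted sensitivity set would also be smaller and less precise.

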## Response evaluation for target lesions

|                             |                                                                                                                                                                                                                                                   |
|-----------------------------|---------------------------------------------------------------------------------------------------------------------------------------------------------------------------------------------------------------------------------------------------|
| CR
(Complete response)   | When all non-lymph node lesions disappear and the short diameters of all lymph node target lesions become < 10 mm.                                                                                                                                |
| PR
(Partial response)    | When the sum of diameters of the target lesions becomes at least 30% smaller than their corresponding sum of diameters at baseline.                                                                                                               |
| SD
(Stable disease)      | When no tumor regression corresponding to PR or tumor enlargement corresponding to PD is observed.                                                                                                                                                |
| PD
(Progressive disease) | When a sum of diameters of a target lesion becomes at least 20% larger than the smallest sum of diameters measured previously and the absolute value of the sum of diameters increases by at least 5 mm (including the incidence of new lesions). |
| NE
(Not evaluable)       | When tests cannot be done for any reason or when a lesion cannot be determined to be any of CR, PR, PD, or SD.                                                                                                                                    |

Reduction rate of the longest sum of diameters = (sum of diameters before treatment - sum of diameters at evaluation) / (sum of diameters before treatment)  $\times$  100%

Increase rate of the longest sum of diameters = (sum of diameters at evaluation - the smallest sum of diameters) / (the smallest sum of diameters)  $\times$  100%

- Actual measurement values of the diameters of target lesions will be recorded as long as they are measurable (for example, even < 5 mm). However, when the diameter of a target lesion is determined as "non-measurable because it is too small", the diameter of the lesion will be recorded as 0 mm if it is determined that none of the tumor lesion remains, or as 5 mm if it is determined that some tumor lesion remains regardless of the slice thickness used for CT.
- When the reduction rate satisfies the condition for PR and the increase rate satisfies the condition for PD at the same time, the lesion will be considered to be PD.
- When lesions separate from a single lesion during treatment, these lesions will be added to each sum of diameters.
- When > 1 lesion fuses together and their boundaries become identifiable during treatment, the diameter of the fused lesion will be added to the sum of diameters. If the boundaries of the lesions are identifiable, the diameter of each lesion will be added to the sum of diameters even if the lesions share a margin.

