## Response evaluation for non-target lesions

|                             |                                                                                                                                                                                                                                       |
|-----------------------------|---------------------------------------------------------------------------------------------------------------------------------------------------------------------------------------------------------------------------------------|
| CR
(Complete response)   | When all non-lymph node lesions disappear, all tumor markers fall within the upper limit of the facility's normal reference values, and the short diameters of all lymph node target lesions become < 10 mm.                          |
| Non-CR/non-PD               | When $\geq 1$ non-lymph node lesions do not disappear, or the short diameters of $\geq 1$ lymph node non-target lesions are $\geq 10$ mm, or $\geq 1$ tumor marker exceeds the upper limit of the facility's normal reference values. |
| PD
(Progressive disease) | "Obvious progression" of non-target lesions (including incidence of new lesions) (see the comments below the table for the definition of obvious progression).                                                                        |
| NE
(Not evaluable)       | When tests cannot be done for any reason, or when a lesion cannot be determined to be any of CR, non-CR/non-PD, or PD.                                                                                                                |

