| Unequivocal PD                 | Yes or No                | PD               |
| Any                            | Yes                      | PD               |

(6) Best overall response

The best overall response will be considered in the order of CR > PR > SD > PD > NE. The overall evaluation at the best time point from the initiation of treatment through to the initiation of post-treatment will be considered to be the best overall response.

Meanwhile, determination of CR or PR in 4-week periods is not necessary in this study. When an overall response corresponds to the definition given for multiple categories, it will be categorized into the best-fitted category in the order of CR > PR > SD > PD > NE.

SD determination shall satisfy the SD standards after 6 weeks from the start of treatment. When an obvious deleterious change (exacerbation) of the disease is observed before the first effect determination, it will be considered to be PD when no imaging determination is implemented and NE when the determination was not conducted because of discontinuation of treatment due to adverse events or rejection by a subject.

(7) Clinical progression

Progression will be determined in accordance with the following criteria when using a method other than those defined in {3.8 (4) Determination of tumor reduction effect} or when progression in unmeasurable lesions is determined. However, progression will not immediately be determined even when a case corresponds to the following criteria but the judgment of a clinical investigator is prioritized. When image assessment is available, the image assessment will be prioritized.

- ① Confirmation of progression by ultrasound: When obvious progression such as emergence of new lesions, increased pleural effusion, etc. is observed by ultrasound.
- ② Confirmation of progression in bone lesion: When increased accumulation of bone is observed by scintigram or PET, or emergence of new lesions is observed in a bone lesion.
- ③ Exacerbation of subjective symptoms: When a clinical investigator determines there to have been progression, such as obvious exacerbation of bone pain in bone metastasis, obvious exacerbation of a sensation of dyspnea in lung metastasis, etc.

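### Two response rules in Protocol 3.8 (4) are miswritten: the fused-lesion rule gives two sums for one condition, and complete response of non-target lesions is tested on target nodes

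*Protocol*

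**What the plan says.** Both rules are in Protocol 3.8 (4).

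**Fused target lesions** (bullets under the target-lesion table). The first sentence reads "When > 1 lesion fuses together and their boundaries become identifiable during treatment, the diameter of the fused lesion will be added", so one diameter is counted. The second reads "If the boundaries of the lesions are identifiable, the diameter of each lesion will be added to the sum of diameters", and it applies even where the lesions share a margin.

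**Non-target lesions** (response table). The CR row requires non-node lesions to have disappeared, tumor markers to be within the facility's normal limit, "and the short diameters of all lymph node target lesions become < 10 mm". The Non-CR/non-PD row is met when any non-node lesion remains, any marker is raised, or one or more "lymph node non-target lesions are" 10 mm or larger.

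These results feed the time point response in 3.8 (5). That response in turn feeds the clinical benefit rate (CBR, primary), PFS and response rate (RR) in 3.9. For CBR, 3.9 (1) lists CR, PR or SD on imaging.

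**The concern.** The two fusion sentences share one condition but give different values, and neither covers lesions that have merged so that no boundary can be seen. The second sentence allows for a shared margin, which suggests the pair was meant as a contrast and that the first sentence lost its negation.

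The CR and Non-CR/non-PD rows should be complementary as to nodes, but they look at different nodes. The CR row repeats the node clause of the target-lesion table.

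Sites record lesion measurements and also the time point response (5.7 (3)). Two sites following the text could therefore code identical scans differently, in outcomes that include the primary one.

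**Working it through.** **(a) Fused lesions**

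Inputs from the target-lesion table: PR needs a sum at least 30% below baseline. PD needs a sum at least 20% above the smallest previous sum and at least 5 mm larger. The lesion sizes are assumed for illustration: two 20 mm lesions, with the baseline also taken as the smallest previous sum.

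- Baseline sum: 20 + 20 = 40 mm.
- PR line: 0.70 × 40 = 28 mm or less.
- PD line: 1.20 × 40 = 48 mm or more. That is an 8 mm increase, so the 5 mm condition is also met.

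Lesions touch and the boundary is visible:

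| Lesions now | Each lesion counted (second sentence) | Assumed fused diameter (first sentence) |
|---|---|---|
| 24 and 24 mm | 48 mm, +20%: PD | 40 mm, 0%: SD |
| 20 and 20 mm | 40 mm, 0%: SD | 28 mm, -30%: PR |
| 20 and 20 mm | 40 mm, 0%: SD | 30 mm, -25%: SD |
| 15 and 15 mm | 30 mm, -25%: SD | 26 mm, -35%: PR |

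The sentences can agree (third line) or disagree (the other lines). If the boundary cannot be seen, neither sentence applies as written.

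**(b) Non-target nodes**

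Assume that non-node lesions are absent or gone and markers are normal. The node sizes are illustrative.

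| Largest target node | Non-target node | CR row as written | Non-CR/non-PD row | CR row if read on non-target nodes |
|---|---|---|---|---|
| none, or 8 mm | 8 mm | met | not met | met |
| none, or 8 mm | 13 mm | met | met | not met |
| 12 mm | 8 mm | not met | not met | met |
| 12 mm | 13 mm | not met | met | not met |

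As written, one combination meets both rows and one meets neither. Read on non-target nodes, every combination meets exactly one row.

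**Effect of (b) on the outcomes**, from the time point tables in 3.8 (5):

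- *Target lesions present.* If the target response is CR, non-target CR gives overall CR and Non-CR/non-PD gives overall PR. If the target response is PR or SD, the overall response is PR or SD either way. RR counts CR and PR, CBR counts CR, PR and SD, and none of these is progression. RR, CBR and PFS do not change.
- *No target lesions.* The overall response is CR or Non-CR/non-PD. Neither is progression, so PFS does not change. RR concerns patients with measurable lesions (3.8, 3.9 (6)), so it does not change. CBR can change, because 3.9 (1) lists CR but not Non-CR/non-PD.

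Patients of the second kind are eligible. Section 6.2 (2) makes no distinction by measurable lesions. Section 3.8 (1) makes nodes of 10 to under 15 mm non-measurable, so 3.8 (3) makes them non-target.

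**Design figure.** The 43 cases per cohort in 7.3 do not depend on this point. An exact binomial test of 30% against 50% with n = 43, rejecting at 19 or more, has one-sided alpha 0.034 and power 0.820, consistent with the stated inputs.

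**The case against.** The strongest reply is that these are two small drafting slips whose meaning can be recovered from the neighbouring sentence and row. Response evaluation is also left to the treating physician (3.8 (4)), so the rules are not a mechanical algorithm. That limits the weight of the point. It does not remove it, because 3.9 ties the outcomes to these criteria and no other section corrects them.

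Several stronger readings are tempting, and the protocol does not support them.

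- *Unchanged nodes are scored CR.* A reader might apply the ordering in 3.8 (6): "it will be categorized into the best-fitted category in the order of CR > PR > SD > PD > NE". That sentence concerns an overall response in several categories, and its list does not contain Non-CR/non-PD. It does not settle a conflict between rows of the non-target table. The Non-CR/non-PD row also names non-target nodes explicitly. CR is one possible reading, so a CR rate of 100% in untreated-like stable nodal disease does not follow.
- *Truly merged lesions become not evaluable.* This is possible but not certain. The first bullet of the same list has actual diameters recorded whenever they can be measured, and a merged mass may be measurable.
- *Both slips distort RR and PFS.* Only (a) can. Even for CBR, the opening definition in 3.9 (1) rests on absence of progression, which an unchanged node satisfies. The effect of (b) arises only through the list of categories in the sentence that follows.

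The sizes used in (a) were chosen to show that disagreement is possible. For two round lesions that only touch, the combined extent equals the sum (24 + 24 = 48 mm; 15 + 15 = 30 mm), and both sentences give the same category. Disagreement needs overlap, flattening or an elongated shape. This objection stands as to frequency.

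**Conclusion.** Both rules are wrong as written and should be corrected.

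- **(a)** One condition has two different sums, and lesions without an identifiable boundary have no stated value. The choice of sentence can move a patient between PR, SD and PD, and so can reach RR, PFS and CBR.
- **(b)** The two rows are not complementary. A non-target node of 10 mm or more meets both when non-node lesions are absent or gone, markers are normal and no target node is 10 mm or larger. No rule clearly resolves this. The consequence is confined to CBR in patients without target lesions.

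The numerical examples rest on assumed lesion sizes. The protocol gives no basis for how often either situation occurs, so no overall effect on CBR can be quoted. No sample size, test or threshold changes.

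**What to change.** In the first sentence of the fusion bullet in 3.8 (4), change the condition to boundaries that are *no longer* identifiable, and keep the second sentence as it stands. In the CR row of the non-target table, change *target* to *non-target* in the lymph node clause, so that it matches the Non-CR/non-PD row. Notify sites of both corrections.

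The cost is two wording changes and one site note. No new data are needed.
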